### Assessing medication adherence

There are different ways of assessing medication compliance. Patient self-reporting relies mainly on a patient’s recall, and is susceptible to bias. Pill count has also been shown to be unreliable especially if patients fail to return the bottles or dumped the pills before the count [35]. Medication possession ratio is commonly used for claims-based adherence measurement. However, it overestimates the true adherence rate particularly when a patient receives an early refill of the medication. The proportion of days covered (PDC), a recent method for calculating adherence, avoids double counting when refills overlap or when oversupply of medication exists [36]. However, it ignores instances when patients refill their prescriptions before finishing the drug.

In a further sub-study, we will compare the four different measures of adherence, to determine which of these provide a more meaningful or reliable information in the local context based on different performance indicators such as the sensitivity, specificity and kappa statistics using PDC as the gold standard. The percentages of adherence between the different measures will be compared via the McNemar’s test.

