### Follow-up and assessments

The assessments and follow-up schedule (with a window period of ±2 months) are summarised in Table 1.

**Table 1 Tab1:** Summary of study procedures and schedule

Study procedures	Visit 1	Visit 2	Visit 3
	Screening/Baseline	Month 6	Month 12
Informed consent	x		
Assess eligibility	x		
SMAQ	x	x	x
BMQ, ASK-12	x		x
Prescription data	x	x	x
Pill count and refill data		x	x
Estrone, estradiol and androstenedione assays	x		x
UPIRTSO event		x	x
Patient log of daily pill taken and weekly SMS		x	x
^a^Check receipt of SMS	x	x	x

^a^Research coordinator will verbally check the status of SMS receipt at each clinic visit

The patients will be followed up half yearly. The SMAQ will be administered at each visit, while the BMQ and ASK-12 questionnaires will be administered at baseline and 1-year. The hormone assays of estrone, estradiol and androstenedione will also be performed at baseline and 1-year.

This trial does not involve any experimental treatment and thus poses no additional risks to patients. Nevertheless, at each follow-up visit, the research coordinator will record any symptom or event that a patient may have experienced that is considered as UPIRTSO (Unanticipated Problems Involving Risks to Subjects and Others) event. These events will be monitored closely using a log book.

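### The adherence sub-study asks which of four measures is most reliable but scores them against one of the four (PDC), so the named indicators cannot answer the question

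*Protocol article*

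**What the plan says.** The section Assessing medication adherence in the Protocol article describes four ways of measuring adherence and gives each a defect.

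- Self-report: "Patient self-reporting relies mainly on a patient’s recall, and is susceptible to bias".
- Pill count: "Pill count has also been shown to be unreliable especially if patients fail to return the bottles or dumped the pills before the count".
- MPR: "it overestimates the true adherence rate particularly when a patient receives an early refill of the medication".
- PDC, after its handling of overlapping refills has been credited: "However, it ignores instances when patients refill their prescriptions before finishing the drug".

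The aim of the sub-study follows: "we will compare the four different measures of adherence, to determine which of these provide a more meaningful or reliable information in the local context". The method is in the same sentence: "based on different performance indicators such as the sensitivity, specificity and kappa statistics using PDC as the gold standard". The section adds a McNemar comparison of the percentages classed as adherent.

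**The concern.** PDC is both a candidate and the standard by which candidates are judged. A gold standard is taken as the truth, yet the section gives no argument that PDC records tablets actually taken and names a way in which it fails. Two consequences follow.

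- PDC cannot rank below any other measure on the three named indicators.
- When another measure classifies a woman correctly and PDC does not, the other measure is charged with the error.

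The sub-study could therefore recommend PDC for local use on circular evidence. It could also report self-report and pill count as less accurate than they are. Self-report here includes the Simplified Medication Adherence Questionnaire (SMAQ), the trial's primary instrument.

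**Working it through.** The document gives no figure for the sub-study, so there is none to reproduce. The first step is an identity. The rest is illustration on assumed accuracies.

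**1. PDC against itself.** All women fall on the diagonal of the 2×2 table, so sensitivity = specificity = kappa = 1. This holds at any true accuracy of PDC and needs no assumption.

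**2. An equally accurate measure X with independent errors.**

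Inputs, all assumed: sensitivity Se = 0.85 and specificity Sp = 0.75 against true adherence, for both PDC and X; true adherence π = 0.70; errors independent given true status. The value 0.70 is midway between the 60% and 80% adherence assumed under Sample size.

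- P(PDC adherent) = π·Se + (1−π)(1−Sp) = 0.595 + 0.075 = 0.670. The same holds for X.
- P(both adherent) = π·Se² + (1−π)(1−Sp)² = 0.50575 + 0.01875 = 0.5245.
- P(both non-adherent) = π(1−Se)² + (1−π)Sp² = 0.01575 + 0.16875 = 0.1845.
- Apparent sensitivity = 0.5245 / 0.670 = 0.78.
- Apparent specificity = 0.1845 / 0.330 = 0.56.
- Observed agreement = 0.5245 + 0.1845 = 0.709. Chance agreement = 0.670² + 0.330² = 0.5578.
- Kappa = (0.709 − 0.5578) / (1 − 0.5578) = 0.34.

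X is exactly as accurate as PDC, yet PDC scores 1, 1 and 1.

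**3. A perfect measure, same inputs.**

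- Sensitivity against PDC = 0.595 / 0.670 = 0.89.
- Specificity = (0.30 × 0.75) / 0.330 = 0.225 / 0.330 = 0.68.
- Observed agreement = 0.595 + 0.225 = 0.820. Chance agreement = 0.670 × 0.70 + 0.330 × 0.30 = 0.568.
- Kappa = (0.820 − 0.568) / (1 − 0.568) = 0.58.

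A measure that is never wrong would still rank below PDC.

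**4. Range.** The formulas of step 2, with Se = Sp = accuracy (assumed) and π across the 60% to 80% of the Sample size section:

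| π | Accuracy of both | Sensitivity vs PDC | Specificity vs PDC | Kappa vs PDC | Kappa vs truth |
|---|---|---|---|---|---|
| 0.60 | 0.80 | 0.714 | 0.636 | 0.351 | 0.590 |
| 0.70 | 0.80 | 0.742 | 0.579 | 0.321 | 0.558 |
| 0.80 | 0.80 | 0.765 | 0.500 | 0.265 | 0.490 |
| 0.60 | 0.90 | 0.845 | 0.786 | 0.631 | 0.793 |
| 0.70 | 0.90 | 0.864 | 0.735 | 0.599 | 0.771 |
| 0.80 | 0.90 | 0.878 | 0.654 | 0.532 | 0.719 |

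In every row the measure looks worse against PDC than it is against the truth.

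**5. MPR, if its errors overlap with PDC's.** Suppose MPR repeats PDC's result in a share s of women and otherwise behaves like X. Then kappa = s + (1−s) × 0.34, which is 0.34 at s = 0 and 0.8 + 0.2 × 0.34 = 0.87 at s = 0.8. The answer is mostly the assumed s, and the document gives no value for it. The model also treats errors as symmetric. The protocol's account of MPR points one way: early refills make it too high, so women would be adherent by MPR and not by PDC. That would keep sensitivity high and lower specificity. Step 5 therefore shows that flattery is possible, not how large it is.

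**The case against.** The strongest defence is that the sentence is loosely worded. Naming a reference and reporting sensitivity, specificity and kappa is a usual way to ask how well other measures agree with it. The list of indicators is open-ended, and McNemar's test needs no reference. The comparison is also peripheral: it is not among the Study objectives, and PDC plays no part in the primary analysis.

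The point about scope stands in full. The rest stands only in part. The stated aim is to choose among the four, not to measure agreement of three with the fourth. McNemar's test can show that two percentages differ, but not which is nearer the truth. No indicator named in the plan judges PDC against anything outside itself.

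A reader might infer more than the document supports:

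- **That MPR is favoured by construction.** The protocol does not say that MPR and PDC use the same records. This is inferred from the way both are described and from the single refill item in Table 1. One-directional error could cost MPR specificity, so second place is not assured.
- **That the whole ranking is settled in advance.** Only PDC's place is. The order of self-report, pill count and MPR depends on the data.
- **That the hormone assays offer a ready replacement standard.** They lie outside the four measures ("The hormone assays of estrone, estradiol and androstenedione will also be performed at baseline and 1-year"), but they mainly reflect recent intake. SMAQ asks about doses skipped in the last week, so its time window would tend to favour it. The Inclusion criteria admit ages 21 to 80 with no menopausal restriction, so levels may also vary for reasons other than tablet taking.

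**Conclusion.** The point holds, at low severity. On sensitivity, specificity and kappa, PDC is perfect by definition, so the plan cannot determine which of the four measures is most reliable. That conclusion needs no assumption.

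The size of the penalty on the other measures does rest on assumptions. With independent errors and equal accuracy it is 0.78, 0.56 and kappa 0.34 in the worked case. Kappa runs from 0.265 to 0.631 over accuracies of 0.80 to 0.90 and adherence of 60% to 80%. Any advantage to MPR is conjecture until its data source is stated.

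A reader might also infer that the trial's main result is at risk because SMAQ is among the measures marked down. The document does not support that: the primary comparison of SMAQ adherence and the sample size do not use PDC.

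**What to change.** Choose one of two wordings for the sub-study.

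1. Keep the comparison of all four measures, but drop the gold-standard label. Report kappa with positive and negative agreement for every pair, and state whether MPR and PDC are computed from the same records. McNemar's test can stay.
2. Keep PDC as the reference, but restate the aim as agreement of self-report, pill count and MPR with PDC, with no claim about which measure is most accurate.

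Under either wording, the association of each measure with Month-12 hormone levels, adjusted for baseline, may be added as exploratory. It should not be the ranking criterion.

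The cost is a change of wording and a few more tables. No visit, sample or data item is added. What is given up is a single declared winner, which the present design could not validly supply.

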### Ethics and dissemination

Informed consent will be obtained by the co-Principal Investigators or research coordinator during the screening visit, prior to randomisation into the trial. The patient’s consent to participate in the trial should be obtained after a full explanation has been given of the intervention options and the manner of intervention allocation. A copy of the signed consent form with study information will be given to the patients for their retention. The right of the patient to refuse to participate without giving reasons must be respected. After the patient has entered the trial, the clinician must remain free to give alternative intervention to that specified in the protocol at any stage if she feels it to be in the patient’s best interest. The patient must remain free to withdraw at any time from the protocol intervention without giving reasons and without prejudicing her further treatment.

The protocol and the associated informed consent documents have been reviewed and approved by the institutional review board of both study sites. The results of this trial will be published in a peer-reviewed journal.

### Data quality assurance

To ensure accuracy, completeness and reliability, the data will be prospectively collected and entered into the electronic database. Hardcopies of the data collection forms will be checked for completeness and verified by the research coordinator before data entry. Validity range checks will also be built into the database. At the study closure, 10% of the records will be randomly sampled for data quality assurance.

### Confidentiality of data and patient records

All data will be treated with strict confidentiality and will not be shared with parties other than members of the investigating team. All data will be centrally coordinated and the hardcopy forms will be kept under lock-and-key in a cabinet in the research coordinator’s office. The softcopy data will be stored in a hard disk and protected by password. Subjects will be identified by a unique trial number and their identities will not be revealed in the data collection forms or questionnaires. A patient study ID list containing patient’s name, personal identification number, mobile phone number and trial number will be maintained and kept in a study folder separate from the data collection forms.

## Discussion

In recent years, various interventions have been utilised to improve medication adherence to AI therapy for breast or other types of cancer [37, 38]. A pilot randomised controlled trial of a web-enabled application to provide real-time monitoring and better management of treatment-related adverse symptoms among patients with hormone-receptor positive breast cancer showed web-enabled application with weekly reminders significantly improved short-term AI adherence. Also, several studies have suggested that short message reminder could benefit adherence to breast self-examination or cancer-screening among breast cancer patients [39, 40]. Chung et al. suggested that self-reported breast self-examination (BSE) adherence and the frequency of BSE were significantly higher in the intervention group than in the control group in the 6-month period [39]. However, to our knowledge, there has not been any study involving short-term clinical outcomes such as hormonal assays from reminders for breast cancer patients on AI therapies.

Studies on breast cancer have demonstrated that patients commonly reported suffering from physical and psychological inconvenience due to AI therapies [41]. As compared to women without a history of cancer, breast cancer patients, reported significantly higher odds of new onset of forgetfulness, difficulty in concentrating, hair loss and numbness or tingling in the extremities after the first 6 months of AI therapy, with odds ratio ranging between 2 to 4 folds [41]. A German study also showed that age contributed to the difference in medication adherence amongst breast cancer women who were treated with AI [42]. It suggested that patients aged over 70 years exhibited a 25% reduction in risk of treatment discontinuation as compared to younger patients. However, a literature review discussing poor adherence with hormonal therapy among women with breast cancer disagreed with the notion that non-adherence could be due to older age (≥55 years). It reported that other reasons for hormonal therapy non-adherence could be due to patient’s behaviour, treatment toxicity, cost of health care or medications, and comorbidities [43]. Also, it has been further suggested that medication compliance may be improved if financial barriers were removed [43]. Meanwhile, other researchers have identified socio-demographic and clinical characteristics to be associated with medication beliefs about AI such as concern, perceived necessity of taking the drug to improve one’s health, and cancer/health worry amongst postmenopausal women [44].

This trial has several strengths as well as limitations. This will be the first study to evaluate short-term clinical outcomes from SMS reminder for breast cancer patients on AI therapy. Random allocation to SMS reminder or control arm ensures that patients in both arms will be comparable with respect to demographic and clinical characteristics, and any difference in outcomes can be attributed to the intervention. However, participants are not blinded to the assignment of intervention, thus there may be potential for bias in outcome assessments.

In short, sending SMS reminder to early-stage breast cancer women could be an added feature to existing healthcare protocol for breast cancer women if the results from our trial are promising. Understanding the potential barriers to medication adherence would enable policy makers to make informed decision when promoting regulations to minimise the impact of the barriers while formulating policies to elevate medication adherence.

## Abbreviations

AI: Aromatase inhibitor
ANCOVA: Analysis of covariance
ASK: Adherence Starts with Knowledge
BMQ: Beliefs about Medicines Questionnaire
BSE: Breast self-examination
ER: Estrogen receptor
NCIS: National University Cancer Institute, Singapore
PDC: Proportion of days covered
SMAQ: Simplified Medication Adherence Questionnaire
SMS: Short message service
UPIRTSO: Unanticipated problems involving risks to subjects and others
